## Introduction

Frailty is a kind of clinical syndrome in older adults who are easily affected by stress. Physical frailty, originally defined by Fried et al. (2001), includes slow gait speed, weakness, self-reported exhaustion, low activity, and weight loss. Due to differences in regions, diagnostic criteria, and other factors, the prevalence of frailty is changed in different parts of the world; previous studies have shown that the prevalence ranged from 4 to 59% and increased with age (Choi et al., 2015; Hoogendijk et al., 2019). It is associated with the development of most chronic diseases, falls, fractures, disabilities, and other adverse outcomes (Theou et al., 2017; Hanlon et al., 2018). Fortunately, frailty is a dynamic reversible process, and measures can be taken to prevent it in advance (Lang et al., 2009).

The health benefits of physical activity have been widely recognized (Cheng et al., 2021). Proper physical activity can improve muscle, heart, and lung function and reduce the risk of high blood pressure, coronary heart disease, stroke, diabetes, cancer, depression, sleep disorders, falls, and fracture (de Labra et al., 2015; Dipietro et al., 2019; Mugueta-Aguinaga and Garcia-Zapirain, 2019). The WHO recommends that adults over 65 years of age engage in at least 150 min of moderate-intensity physical activity per week or at least 75 min of vigorous-intensity physical activity per week, or a combination of moderate and vigorous-intensity physical activity to achieve this amount of physical activity, with at least 10 min of continuous activity each time (van der Ploeg and Bull, 2020).

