120–150	≥150		5 days, 1 time/day, 30 min/time					

**TABLE 2 T2:** List of physical activities available to participants.

01. Walking quickly	11. Badminton	21. Plank support
02. Running	12. Table tennis	22. Pushups
03. Tai Ji	13. Volleyball	23. Sit-ups
04. Skipping rope (≥100 time/min)	14. Football	24. Pull-ups
05. By bike (outdoor > 8 km/h)	15. Basketball	25. Lunge
06. By bike (gym > 8 km/h)	16. Tennis	26. Jumping jacks
07. Upstairs	17. Swimming	27. Squat
08. Downstairs	18. Martial arts	28. Pilates
09. Wash the car	19. Skating	29. Aerobic dance
10. Do housework	20. Skiing	30. Yoga

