##### Frail Score

The frailty phenotype represents the most known operational definitions of frailty in older persons (Fried et al., 2001). According to the Fried phenotype: 0 = health; 1–2 = pre-frailty; and ≥ 3 = frailty. Walking speed, grip strength, weight, physical activity, and self-reported fatigue will be measured by the methods as shown in Table 3. One point will be recorded when any items reach the cutoff value.

**TABLE 3 T3:** Indicators collected and assessment tools at each time point.

Test	Content				Time point				
					Screen	Baseline		12 w	24 w
FRAIL	The simple “FRAIL” questionnaire screening tool				√					
	Fatigue	Are you fatigued?							
	Resistance	Cannot walk up one flight of stairs?							
	Aerobic	Cannot walk one block (500 m)?							
	Illnesses	Do you have more than 5 illnesses?							
	Loss of weight	Have you lost more than 5% of your weight in the last 6 months?							
	Scoring: 3 or greater = frail; 1 or 2 = prefrail								
Demographic	Standardized questionnaire assessing age, gender, education level, residential status, falls history, medical history and so on.					√		√	√
Gait	Gait parameters generated by the device					√		√	√
TUG	Timed up and go test					√		√	√
Fried	Scoring: 3 or greater = frail; 1 or 2 = prefrail; 0 = health					√		√	√
	Walking speed	Slow gait: < 1.0 m/s							
	Grip strength	Measure three times and take the optimum							
		Low grip strength as follows:							

		**Males**		**Females**					
		**BMI**	**Grip strength (kg)**	**BMI**	**Grip strength (kg)**				

		≤24	≤29	≤23	≤17				
		24.1–28	≤30	23.1–26	≤17.3				
		≥28	≤32	26.1–29	≤18				
	Weight loss	Methods: measure three times and take the average, after urination in the morning							
		Weight loss: an unintentional weight loss ≥ 10 kg/10% over the previous year or an average monthly loss ≥ 1 kg/1%							
	Insufficient physical activity	≤150 min of light to moderate physical activity per week, or ≤ 75 min of vigorous physical activity per week, or the total level of physical activity did not achieve the same amount of expenditure							
	Fatigue	Asking question “Do you feel too weak to do what you want to do in the last month?” If the participants answered “yes,” they will be considered fatigued							
MVPA	Short International Physical Activity Questionnaire						√	√	√
	High	Meet any one of the following 2 standards							
		Vigorous activity ≥ 3 days and total level ≥ 1,500 MET							
		The total physical activity ≥ 7 days and 3,000 MET-min/w							

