	Sufficient	Meet any one of the following 3 standards							
		Vigorous activity ≥ 20 min per day and total ≥ 3 days							
		Moderate and/or walking ≥ 30 min per day and total ≥ 5 days							
		The total physical activity ≥ 5 days and 600 MET-min/w							
	Low	Meet any one of the following 2 standards							
		No activity was reported							
		Some activities reported, but not meet the criterion of the above sufficient and high							
PHQ-9	Patients Health Questionnaire 9-item						√	√	√
GAD-7	Generalized Anxiety Disorder 7-item						√	√	√
MMSE	Mini-Mental State Examination						√	√	√
PSQI	Pittsburgh Sleep Quality Index						√	√	√

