##### Moderate-to-Vigorous-Intensity Physical Activity Per Week (MET-Min/Week)

Moderate-to-vigorous-intensity physical activity (MVPA) will be evaluated by the International Physical Activity Questionnaire (IPAQ) (Bassett, 2003). The IPAQ Questionnaire comprises 7 questions about the frequency and duration of vigorous activity (8 MET), moderate activity (4 MET), walking (3.3 MET), and sitting. The total physical activity will be calculated by multiplying the time (minutes per week) by the intensity [metabolic equivalent of task (MET) unit]. Its effectiveness in evaluating the physical activity level has been verified in various populations in China (Hu et al., 2015; Ren et al., 2017). Data processing principle: the cutoff value of the daily time of a certain intensity physical activity is 180 min; if the total daily time of three intensities physical activity is > 960 min (16 h), data will be excluded from the analysis; if the daily time of a certain intensity physical activity is < 10 min, the time and corresponding weekly frequency will be recorded as 0.

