##### Other Secondary Outcomes

The difference between the percentage of walking speed < 0.6m/s, gait variability > 3%, frailty score ≥ 3, and low physical activity will also be compared.

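### The Fried score's low-activity item joins its three shortfalls with 'or', so read literally almost every participant scores the point, including after 300 minutes of moderate activity a week

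*Protocol article*

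**What the plan says.** Under Frail Score, each of the five Fried items is scored by a cutoff in Table 3: "One point will be recorded when any items reach the cutoff value". A total of 3 or more is frailty. The low-activity item is met by "≤150 min of light to moderate physical activity per week, or ≤ 75 min of vigorous physical activity per week". A third alternative, also joined by 'or', is a weekly total that falls short of the equivalent expenditure.

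Three other places bear on the same quantity:

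- The Introduction gives the recommendation as "at least 150 min of moderate-intensity physical activity per week or at least 75 min of vigorous-intensity physical activity per week". It also accepts an equivalent mix of the two.
- The top row of Table 1 (target at least 150 min a week) is delivered as "5 days, 1 time/day, 30 min/time".
- The MVPA part of Table 3 classes a week as Sufficient on any one of three criteria, one of which is "Moderate and/or walking ≥ 30 min per day and total ≥ 5 days".

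Other Secondary Outcomes compares between groups the percentage with "frailty score ≥ 3". Table 3 schedules the FRAIL questionnaire at screening only, so the Fried score is the only frailty measure at 12 and 24 weeks.

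**The concern.** The recommendation is met by A, or B, or an equivalent mix. Not meeting it is therefore not-A and not-B and not-mix. Table 3 writes not-A or not-B or not-mix, which is a much wider condition: missing either minute threshold is enough, however much activity of the other kind is done.

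This is the Fried item that a physical activity programme acts on most directly. If nearly everyone scores it at every visit, a real rise in activity does not show in the frailty score, and the comparison of scores of 3 or more has to rest on the other four items. The Conclusion expects the programme to delay or reverse frailty, and this score is the measure that would show it.

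**Working it through.** **Inputs.** Thresholds of 150 and 75 min and the 'or' (Table 3, Fried block). Weights of 8, 4 and 3.3 MET for vigorous activity, moderate activity and walking (MVPA section). Schedule in Table 1. The document does not put a number on the equivalent expenditure; I take it from the two thresholds.

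**Step 1: the plan's own figures.** Top row of Table 1: 5 × 30 = 150 min, which reproduces its target. Equivalent expenditure: 150 × 4 = 600 and 75 × 8 = 600 MET-min, so the two thresholds agree.

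**Step 2: apply the rule.** The last column requires all three shortfalls, with strict limits and walking counted as light-to-moderate.

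| Week (min) | As written | All three required |
|---|---|---|
| 149 moderate, 0 vigorous | point | point (149 × 4 = 596 < 600) |
| 150 moderate, 0 vigorous | point | none |
| 300 moderate, 0 vigorous | point (0 ≤ 75) | none |
| 0 moderate, 150 vigorous | point (0 ≤ 150) | none |
| 150 walking, 0 vigorous | point | none |
| 151 moderate, 76 vigorous | none | none |

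The last row is the lowest whole-minute combination that escapes the written rule. With moderate activity it costs 151 × 4 + 76 × 8 = 1,212 MET-min, about twice 600.

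**Step 3: which defect matters.** Changing ≤ to < and keeping 'or' changes little: 150, 200 or 300 min of moderate activity with no vigorous activity still scores, because 0 < 75. The 'or' is the main fault. The inclusive limit matters only at exactly 150 min. Even with 'and', 150 min of walking is 150 × 3.3 = 495 MET-min, below 600, and would score if the limit stayed at ≤150. The MVPA block calls that same week Sufficient when it is done as 30 min on 5 days.

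**Step 4: size of the loss.** Let q be the proportion scoring the item under a working rule, and X the number of the other four items present. Then P(score ≥ 3) = P(X ≥ 3) + q × P(X = 2). If X has the same distribution in both groups, the between-group difference is (gap in q) × P(X = 2). When everyone scores the item, q = 1 in both groups and this difference is zero.

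The inputs are assumptions: four independent items, each with prevalence p, so P(X = 2) = 6p²(1 − p)².

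| p | P(X = 2) | Gap 20 points | Gap 50 points |
|---|---|---|---|
| 0.2 | 0.154 | 3.1 | 7.7 |
| 0.4 | 0.346 | 6.9 | 17.3 |
| 0.5 | 0.375 | 7.5 | 18.8 |
| 0.7 | 0.265 | 5.3 | 13.2 |

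The last two columns are percentage points. As a check, take p = 0.4 with q of 0.8 in controls and 0.3 in group 1. P(X ≥ 2) = 0.525 and P(X ≥ 3) = 0.179. Controls: 0.8 × 0.525 + 0.2 × 0.179 = 0.456. Group 1: 0.3 × 0.525 + 0.7 × 0.179 = 0.283. The difference is 0.173. With the point always scored, both groups are at 0.525.

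**The case against.** The best defence is that the 'or' is loose wording in a condensed table and merely lists the arms of the recommendation. The third clause supports this. Under a literal 'or' it can never add a case, because anyone above both minute thresholds has at least 150 × 3.3 + 75 × 8 = 1,095 MET-min, well over 600. It has a function only if all three shortfalls are required. That makes the intended meaning likely, but it also shows that the sentence is misdrafted. It is a stated scoring rule, and an analyst who codes it as printed gets a near-constant item.

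Several limits on the consequences stand:

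- A reader might infer that the item cannot move at all. It can, for anyone who exceeds both thresholds.
- A reader might infer that the activity response is lost to the trial. It is not: MET-min per week is a separate outcome, and the percentage with low activity is compared separately.
- A reader might infer bias. A point added to nearly everyone in both groups reduces sensitivity but does not favour either arm.
- The other four items can still move the score across 3.
- The 150-min boundary is narrow. The Table 1 target is at least 150, and the questionnaire also picks up activity outside the schedule.

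**Conclusion.** The concern holds as an error in a stated scoring rule for one item of a secondary outcome. As printed, the item contradicts the recommendation in the Introduction. It also calls 30 min of moderate activity on 5 days insufficient, while the MVPA block of the same table calls that week Sufficient. The consequence is reduced sensitivity of the Fried score and of the comparison of scores of 3 or more. The TUG primary outcome is not affected.

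The size cannot be fixed from the document. Across item gaps of 20 to 50 points and prevalences of 0.2 to 0.7, the difference removed runs from about 3 to about 19 percentage points. This assumes independent items and no effect on the other four. A reader might settle on 17 points as the amount hidden. That is one scenario near the upper end and should not be quoted alone. The logical error itself needs no assumption; the near-constancy assumes only that few frail older adults exceed both thresholds every week.

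**What to change.** Rewrite the item in Table 3 so that the point is scored only when all three hold:

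1. questionnaire walking plus moderate minutes are below 150 a week;
2. vigorous minutes are below 75 a week;
3. the combined total is below the equivalent amount, stated as a number (600 MET-min follows from the protocol's own thresholds and weights).

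Counting walking in the first condition is needed. If only moderate minutes counted, 5 × 30 min of walking (495 MET-min) would still score the point while being Sufficient in the MVPA block. With walking counted, the item agrees with the top row of Table 1 and with the 30-min, 5-day criterion.

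One mismatch remains. The MVPA block also accepts 20 min of vigorous activity on 3 days: 3 × 20 = 60 min and 60 × 8 = 480 MET-min, which would still score the point if done alone. The sponsor should say whether that difference between the two classifications is intended.

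The cost is a short text change made before the Fried score is computed. The questionnaire is scheduled at baseline, 12 and 24 weeks, so no new data are needed.

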##### Moderate-to-Vigorous-Intensity Physical Activity Per Week (MET-Min/Week)

Moderate-to-vigorous-intensity physical activity (MVPA) will be evaluated by the International Physical Activity Questionnaire (IPAQ) (Bassett, 2003). The IPAQ Questionnaire comprises 7 questions about the frequency and duration of vigorous activity (8 MET), moderate activity (4 MET), walking (3.3 MET), and sitting. The total physical activity will be calculated by multiplying the time (minutes per week) by the intensity [metabolic equivalent of task (MET) unit]. Its effectiveness in evaluating the physical activity level has been verified in various populations in China (Hu et al., 2015; Ren et al., 2017). Data processing principle: the cutoff value of the daily time of a certain intensity physical activity is 180 min; if the total daily time of three intensities physical activity is > 960 min (16 h), data will be excluded from the analysis; if the daily time of a certain intensity physical activity is < 10 min, the time and corresponding weekly frequency will be recorded as 0.

##### Psychological Condition

Patients’ psychological condition will be reflected by anxiety, depression, and sleep quality. Anxiety will be evaluated by the Generalized Anxiety Disorder 7-item (GAD-7) Scale within 7 questions and a total score of 0–21 (Spitzer et al., 2006). Depression will be assessed by the Patients Health Questionnaire 9-item (PHQ-9) within 9 questions and a total score of 0–27 (Kroenke et al., 2001). The Pittsburgh Sleep Quality Index (PSQI) will be used to evaluate the sleep quality in the last month, which consists of 19 self-report items and 5 other-report items; the 19th self-report item and 5 other-report items will not be scored. The total score ranged from 0 to 21; the higher the score, the worse the sleep (Liu et al., 2021).

##### Cognitive Function

The Mini-Mental State Examination (MMSE) is one of the standardized intelligence examination tools and is widely used in the screening of Alzheimer’s disease (Folstein et al., 1975). Cognitive function will be evaluated by testing their orientation, memory, attention, calculation, recall, and language ability. The total score is related to education level with a range of 0–30.

##### Adherence and Security

If 9 weeks and more reach to the target activity levels during the entire intervention period, it will be considered as good adherence. The incidence of adverse events, including falls and all-cause hospital admissions, will be assessed by patient self-report.

##### Other Secondary Outcomes

The difference between the percentage of walking speed < 0.6m/s, gait variability > 3%, frailty score ≥ 3, and low physical activity will also be compared.

### Statistical Analysis

Categorical variables will be described by frequency and percentage. Continuous variables will be described by means and standard deviations. Social demographic and clinical data between the groups will be presented using appropriate descriptive statistics and evaluated for homogeneity using independent *t*-test, Mann-Whitney, chi-square, and Fisher’s exact tests, as appropriate. The differential changes of the primary and secondary outcomes at T1 and T2 concerning T0 between the two groups will be assessed using generalized estimating equations (GEE). The baseline variable will be adjusted, and group effects, time effects, and interaction effects will be observed. DSS statistics 25 will be used for data analysis, and *P* < 0.05 will be considered statistically significant.

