#### Calculation of Sample Size

Based on *a priori* power analysis (G*Power 3.1.9.3) using a power of 0.90 and error probability of 0.05, a sample size of 50 participants will be required for each group to detect an assumed 20% difference in walking speed between the two groups. In addition, with an assumption of 15% dropout rate, a sample size of 120 participants will be initially targeted.

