#### Primary Outcome

##### Physical Function

The physical function will be evaluated by the Timed Up & Go (TUG) test (Mathias et al., 1986), which assesses the basic mobility skill as well as strength, balance, and mobility. In this test, the subjects will stand up from a standard chair (the chair with a height of 46 cm and arms with a height of 65 cm), wear comfortable shoes, walk at a regular speed of 3 m, turn around, walk back to the chair, and sit down in the chair, and then will stop the timer. According to the test results, ≤ 10 s will be considered completely independent, 10–19 s will be considered to be independent, between 20 and 29 s will be considered a “gray area,” and more than 30 s will be considered to be completely dependent. Its reliability and effectiveness have been verified in various populations (Chan et al., 2017; Yuksel et al., 2017).

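### GEE is the only outcome model and 15% dropout is expected; without weighting or imputation the week-24 Timed Up & Go contrast is open to bias, of a size that depends on how baseline enters the model

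*Protocol article*

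**What the plan says.** The Statistical Analysis section of the protocol article names one model for all outcomes: "The differential changes of the primary and secondary outcomes at T1 and T2 concerning T0 between the two groups will be assessed using generalized estimating" (that is, by GEE). The next sentence reads: "The baseline variable will be adjusted, and group effects, time effects, and interaction effects will be observed". The section states no working correlation, weighting or imputation.

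Calculation of Sample Size expects loss: "with an assumption of 15% dropout rate, a sample size of 120 participants will be initially targeted". The 15% is a single figure, not divided by arm, visit or reason, and its only use is to raise the recruitment target.

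Primary Outcome makes TUG the measure of physical function. Study Design places assessments at baseline, 12 and 24 weeks, with the intervention ending at week 12 and a 12-week follow-up after it. The Introduction makes the lasting effect part of the aim, so the week-24 comparison matters.

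**The concern.** GEE estimated from the available rows is protected when data are missing completely at random, or when loss depends only on covariates that are correctly in the mean model. It has no general protection when loss depends on an earlier outcome that is not conditioned on. A likelihood model with the right mean and covariance has that protection under missing at random.

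Participants are frail and aged 65 or over, and only group 1 has weekly activity targets, insoles and uploads. It is plausible, though nowhere stated, that loss is related to TUG and that the relation differs by arm. If slower people leave group 1 more often than slower people leave group 2, those who remain in group 1 look faster and a benefit appears that is not real.

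The baseline sentence can be read in two ways. It may mean that baseline TUG is a covariate and the outcomes are the two later visits. Or changes relative to T0, with group, time and interaction terms, may mean that T0 is itself a row of the outcome. The exposure differs several-fold between the two.

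**Working it through.** The plan's own figure. 50 / (1 − 0.15) = 58.8, so 59 per arm and 118 in total, against 120 stated (also 6 centres × 20). Expected completers: 120 × 0.85 = 102. The dropout allowance is consistent.

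Assumed inputs; the article gives none of these. TUG SD 5 s; correlations 0.7 (T0 with T1), 0.6 (T0 with T2) and 0.7 to 0.75 (T1 with T2); 15% loss per arm, random in group 2 and related to TUG in group 1 with log-odds 0.5, 1 or 1.5 per SD; independence working correlation unless stated. Lower TUG is better, so a negative bias favours the intervention.

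Step 1, shift among those who stay. Integrating the logistic loss model over a standard normal, with 15% lost, gives a mean TUG among stayers of δ = −0.073, −0.133 and −0.175 SD for the three slopes.

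Step 2, T0 as an outcome row, loss on T0. The change compares stayers at T1 with everyone at T0, so bias = 0.7 × 5 s × δ:
- 0.7 × 5 × (−0.073) = −0.25 s
- 0.7 × 5 × (−0.133) = −0.46 s (−0.47 s from the rounded δ)
- 0.7 × 5 × (−0.175) = −0.61 s

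Step 3, baseline TUG as covariate, all loss after week 12 and dependent on T1. Adjustment removes the part of the T2 shift that passes through T0. Bias ≈ (r12 − r02 × r01) × 5 s × δ. With r12 = 0.75 the multiplier is 0.75 − 0.6 × 0.7 = 0.33:
- 0.33 × 5 × (−0.073) = −0.12 s
- 0.33 × 5 × (−0.133) = −0.22 s
- 0.33 × 5 × (−0.175) = −0.29 s

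Simulation of this case (4,000 null trials per scenario, 60 per arm) gave −0.13, −0.22 and −0.31 s with standard errors of about 0.77 to 0.82 s. The largest is 0.31 / 0.77 = 0.40 of a standard error. Further simulation under similar assumptions gave 0.06 to 0.27 s, and 0.25 to 0.62 s at week 24 with T0 as an outcome row. The likelihood estimate was off by about 0.01 s.

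Step 4, large-sample check (150,000 per arm, true effect −0.5 SD, T1–T2 correlation 0.7, 15% loss split evenly before and after week 12, Monte Carlo error about 0.005 SD). Week-24 bias in SD units, with seconds at SD 5 s in brackets:

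| How loss depends on TUG | Independence, T0 as outcome row | Independence, baseline as covariate | Exchangeable or unstructured, baseline as covariate |
|---|---|---|---|
| Previous TUG, equally in both arms, log-odds 1 | 0.000 | 0.000 | 0.000 |
| Baseline TUG, group 1 only, log-odds 1 | −0.085 (0.43 s) | 0.000 to +0.008 (up to 0.04 s) | 0.000 to +0.010 (up to 0.05 s) |
| Previous TUG, group 1 only, log-odds 1 | −0.087 (0.44 s) | −0.014 to −0.020 (0.07 to 0.10 s) | −0.001 to +0.006 (up to 0.03 s) |
| Previous TUG, opposite in the two arms, log-odds −1 and +1 | −0.190 (0.95 s) | −0.035 to −0.048 (0.18 to 0.24 s) | −0.010 to +0.005 (up to 0.05 s) |

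In the third row, week-12 bias was −0.049 SD (0.25 s) with T0 as an outcome row, and −0.002 to −0.006 SD (0.03 s or less) with baseline as covariate. In a deliberately extreme case (log-odds −2 and +2) the covariate model under independence reached −0.053 to −0.078 SD (0.27 to 0.39 s).

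**The case against.** The strongest reply is that the article already adjusts for baseline. This stands in large part: with baseline TUG as a correctly modelled covariate, baseline-related loss is nearly harmless, and so is the week-12 contrast. It does not close the matter, because the article does not say that the baseline variable is TUG or that it enters as a covariate.

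A second reply is that unweighted GEE and an independence correlation are read from silence, and a condensed article may leave such details to a fuller document. That stands: the missing detail is not itself the fault. The point rests on the stated choice of GEE, for which a more robust alternative is available at little cost.

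A third is that group-specific dependence is assumed. The 15% is one overall figure, and with equal dependence the contrast was unbiased to within about 0.03 s. The programme also ends at week 12, so the loss that matters most comes when the exercise load is over. Both remarks are fair. They make the size uncertain, but do not rule out the mechanism.

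A reader might infer more: that people who stop exercising go untested, or that those who cannot complete TUG become missing. The documents support neither. Under Intervention, the assessments are to be repeated at both later visits, and adherence is defined separately. The phrase "more than 30 s will be considered to be completely dependent" classifies a recorded time, not an absent one.

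**Conclusion.** The point holds in limited form. GEE is the only stated model, 15% loss is expected, and GEE without weighting or imputation has no general validity when loss depends on earlier observed outcomes.

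- Baseline TUG as covariate: the remaining exposure is the week-24 contrast, about 0.06 to 0.3 s in favour of the intervention and up to about 40% of a standard error. This needs both an independence working correlation and loss after week 12 that depends on week-12 TUG differently by arm. It is near zero with an exchangeable or unstructured correlation, or with equal dependence.
- T0 as an outcome row, under independence and with dependence in group 1 only: about 0.25 to 0.6 s, at both visits.

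The SD, correlations, loss slopes and split of loss are all assumptions. One might conclude that the analysis is unbiased only if loss is unrelated to any earlier TUG, or that both visits are necessarily affected. The baseline adjustment and the results above do not support either. The reassurance about working correlation was checked for continuous outcomes only, not for the percentages listed under Other Secondary Outcomes.

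**What to change.** For TUG and the other continuous outcomes, use a likelihood-based mixed model for repeated measures with unstructured covariance and terms for visit, group, group-by-visit and baseline value by visit. Include all randomised participants with any post-baseline value.

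Alternatively keep GEE, name baseline TUG as a covariate, and run it after multiple imputation by arm that uses baseline and 12-week values. For the percentage outcomes, keep GEE after the same imputation.

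The cost is a change of wording; the methods are in standard software and need no extra data. The downside is small: the mixed model assumes approximate normality and missing at random, so it does not protect against loss that depends on unobserved TUG.
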